##### Patient environmental inclusion criteria:

- Lives in a rural area (see definitions in Appendix) that can be served by the RHH team.
- Has capacity to consent to study OR can assent to study and has proxy who can consent (see subject enrollment, below)
- Can identify a potential caregiver who agrees to stay with patient for first 24 hours of admission. Caregiver must be competent to call care team if a problem is evident to her/him. After 24 hours, this caregiver should be available for as-needed spot checks on the patient.
  - This criterion may be waived for highly competent patients at the patient and clinician's discretion.

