#### Patient caregiver inclusion criteria: (not required for patient participation):

- Age  $\geq 18$  years old
- Has capacity to consent to study
- Lives within 15 minutes travel time.

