#### **5.5 Data to be collected and when the data will be collected**

For both groups we will administer a survey to patients on admission, at discharge, and 30-days post-discharge. For both groups, we will administer a survey to caregivers at admission and 30-days post-discharge.

For the intervention arm only, within 30-days of discharge we will conduct qualitative interviews with the patient and their caregiver (if their caregiver consented to participate in the study, caregiver participation is not required for patient enrollment in this study) (please see more details below).

For the intervention arm, we will ask the rural home hospital MD to complete the MD AM Report each morning and the RHH RN/EMT-P to complete the Nursing visit form after each patient visit. Twice a week we will send the RHH clinicians the Clinician process measures survey. Post-discharge we will conduct qualitative interviews with rural home hospital clinicians only (please see more details below).

For both groups:

Clinical and administrative data will be extracted from electronic sources (e.g., enterprise data warehouse, electronic health record (EHR) at study sites). Cost data for the hospitalization and post-discharge period will be obtained from study site financial personnel using direct cost accounting methods. We will also collect information from patients and caregivers using IRB approved surveys and standardized questionnaires (see below). All data will be collected by trained study staff and inputted on a Partners encrypted shared drive. Data collected from filed research collection (including patient surveys) will be stored in REDCap (Research Electronic Data Capture, Vanderbilt University, Nashville, TN), which is fully HIPAA-compliant secure web application.

- All data collected at Alberta Health Services (Wetaskiwin Hospital) will also be stored on MGB REDCap

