#### 5.5.2 Secondary endpoints

| Measure                                                                                                       | Source                     | Day(s) Obtained         |
|---------------------------------------------------------------------------------------------------------------|----------------------------|-------------------------|
| Total cost, discharge to 30-days post discharge (published as percent change given sensitivity of these data) | Hospital accounting system | 30 days after discharge |
| Unplanned readmission within 30-days of discharge, %                                                          | EHR and patient report     | 30 days after discharge |
| Days at home (the number of days spent at home from the day of discharge to 30-days later)                    | EHR and patient report     | 30 days after discharge |
| Percent of day lying down                                                                                     | Biometric monitor          | Each day of             |

|  |  |           |
|--|--|-----------|
|  |  | admission |
|--|--|-----------|

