| Follow up with patient's PCP within 14 days, y/n       | RA via pt phone call, cross checked with EHR data                                 | +30             |
| SNF utilization, days                                  | As above.                                                                         | +30             |
| Home health utilization, days                          | As above.                                                                         | +30             |
| Unplanned readmission(s) after index, # and y/n + date | As above.                                                                         | +30             |
| ED observation stay(s), # and y/n + date               | As above.                                                                         | +30             |
| ED visit(s), # and y/n + date                          | As above.                                                                         | +30             |

RA: Research assistant

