|                                        |                                                              |           |
|----------------------------------------|--------------------------------------------------------------|-----------|
| MRSA                                   | As above.                                                    | Daily     |
| New arrhythmia                         | As above.                                                    | Daily     |
| Hypokalemia                            | As above.                                                    | Daily     |
| Acute kidney injury                    | As above.                                                    | Daily     |
| Medication error                       | As above.                                                    | Daily     |
| Unanticipated mortality                | As above.                                                    | Daily     |
| Loss of consciousness                  | As above.                                                    | Daily     |
| Transfer back to hospital a | RA via MD/RN                                                 | Discharge |
| Unplanned mortality during admission   | RA via MD/RN for home patients; MD EHR review for inpatients | Discharge |
| Unplanned 30-day mortality             | RA via pt/caregiver call                                     | +30       |

a: intervention arm only

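### The 30-day mortality row names only a call to the patient or caregiver as its source, without the EHR cross-check that the day-30 utilisation outcomes have

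*Protocol*

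**What the plan says.** The Safety table in section 5.5.3 (exploratory endpoints) lists unplanned 30-day mortality, obtained at day 30, with the source "RA via pt/caregiver call". In the same table, unplanned mortality during admission has the source "RA via MD/RN for home patients; MD EHR review for inpatients".

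The other day-30 event outcomes have a record source. In the Health Care Utilization table, PCP follow-up is obtained by "RA via pt phone call, cross checked with EHR data", and the rows below it (SNF and home health use, readmission, observation stays and ED visits) take the same source. In section 5.5.2, 30-day readmission and days at home come from "EHR and patient report".

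On caregivers, the heading of the caregiver inclusion criteria in section 3.1 says "not required for patient participation", and section 5.5 repeats that "caregiver participation is not required for patient enrollment in this study". Separately, the patient environmental criteria require that the patient "Can identify a potential caregiver who agrees to stay with patient for first 24 hours of admission", with availability for spot checks afterwards. They then add: "This criterion may be waived for highly competent patients at the patient and clinician's discretion".

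**The concern.** Death is the one day-30 outcome for which the patient can never be the informant. With a call as the sole named source, finding a death depends on reaching someone else, and nothing in the protocol secures such a contact at day 30. A death that the call does not find looks the same as a survivor who did not pick up.

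At stake is a downward bias in a safety measure, in a trial that moves acute care into the home and also admits patients on an end-of-life pathway. If deaths are found more readily in one arm than in the other, the comparison between arms is biased as well as the level.

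**Working it through.** The protocol gives no figure for this outcome, so there is nothing to reproduce. The check is a comparison of the text, followed by one calculation for scale.

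**Sources compared**

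| Outcome | Place in protocol | Record source named? |
|---|---|---|
| Mortality during admission | 5.5.3, Safety | Clinical staff (home); EHR review (inpatients) |
| 30-day readmission, days at home | 5.5.2 | Yes, EHR plus patient report |
| PCP follow-up, SNF and home health days, readmissions, ED visits | 5.5.3, Health Care Utilization | Yes, call cross-checked with EHR |
| Unplanned 30-day mortality | 5.5.3, Safety | No, call only |

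The day-30 questionnaires also rest on the patient alone, but that is unavoidable for self-report. Among day-30 events that leave a record, mortality is the exception.

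**Is a caregiver contact assured at day 30?** No. Enrolment of the caregiver in the study is optional. Identifying a caregiver is an eligibility criterion, but it concerns the first 24 hours and spot checks afterwards, and it can be waived.

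**Do other sections supply the missing source?** Only in part.

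- Section 5.5 says that clinical and administrative data for both groups are extracted from electronic sources. It does not name day-30 vital status.
- Section 9.0 says that safety data are taken from medical records and retrieved every 6 months. It does not name day-30 vital status either.
- The list of events for committee review in section 9.0 includes death during admission, not death after discharge.
- No section says how a patient who cannot be reached at day 30 is classified.

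**Could ascertainment differ by arm?** Both arms get the same day-30 patient and caregiver surveys. Section 5.5 adds post-discharge interviews with patient and caregiver in the intervention arm only. That is one more contact through which a death could come to light. The protocol gives no basis for its size.

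**Scale**

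- Input: the recruitment target of 75 patients per arm (section 6.1, Power analysis).
- Effect of one missed death on that arm's rate: 1/75 = 0.0133, or 1.3 percentage points.
- Assumption, not from the protocol: unplanned 30-day mortality of 2% to 10%. Expected deaths per arm are then 75 × 0.02 = 1.5 to 75 × 0.10 = 7.5. One missed death would be 1/1.5 = 67% of the expected deaths in an arm at the low end and 1/7.5 = 13% at the high end.

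**The case against.** The strongest reply is that the row should not be read in isolation. The EHR is already consulted at day 30 for readmission, days at home and ED visits, in both arms, and safety data are drawn from medical records every 6 months. A death in a site hospital or ED would probably be seen there. The row also does not restrict the call to enrolled caregivers, and most patients will have identified one to be eligible. The protocol refers to a Monitoring Plan that is not shown and may say more. The measure is exploratory.

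Much of this stands, and it rules out several stronger readings that a reader might infer:

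- *That a call is the protocol's only route to a death.* This is true of the row but not of the protocol, given the general record extraction.
- *That patients have only an optional caregiver.* What is optional is the caregiver's enrolment as a participant; identifying a caregiver is an eligibility criterion unless waived.
- *That missed deaths would become losses to follow-up.* No section says that unreached patients are classed this way.
- *That a quarter to a half of deaths would be missed.* Such a figure only restates an assumed 25% to 50% share of patients without a reachable caregiver. The protocol gives no such share, and the figure also supposes that none of these deaths appears in the records.
- *That readmission and days at home are corrupted.* Both already use the EHR. At most, a death outside the site's records could affect days at home.

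What the reply does not remove is the gap itself. The general provisions do not name day-30 vital status, and the one row that does leaves out the check that comparable rows have.

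**Conclusion.** The point holds as a weakness in how one exploratory safety outcome is ascertained. Deaths after discharge in patients with no reachable caregiver could be missed or counted as non-response unless the general record extraction happens to find them. Loss that differs by arm is plausible because of the intervention-only interviews, but it is not shown.

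The size is unknown, because the documents give neither a mortality rate nor a share of unreachable patients. The figure of 1.3 percentage points per missed death rests only on 75 patients in an arm; the percentages of expected deaths rest on the assumed 2% to 10%. The primary cost analysis is not affected by this row. The change is still worth making: it costs almost nothing, and a death that goes unnoticed may not be recoverable later.

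**What to change.** In the Safety table, extend the source for unplanned 30-day mortality so that the call to patient or caregiver is cross-checked with EHR data, as in the Health Care Utilization table, and apply it identically in both arms. Require an EHR vital-status check for every patient not reached at day 30. Report those whose status is still undetermined, by arm, as unknown vital status, and do not count them as alive.

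The cost is one table entry and slightly more chart review, since the EHR is already consulted for other day-30 outcomes. The remaining limit is that deaths outside the site's records may still be missed; reporting unknown status by arm makes the possible extent of that visible.

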### Quality: High-Value Care

| Measure                            | Source                                                       | Day(s) Obtained |
|------------------------------------|--------------------------------------------------------------|-----------------|
| Pain management                    | RA via MD/RN for home patients; RA EHR review for inpatients | Daily           |
| Hours of sleep per day             | RA via activity tracker                                      | Daily           |
| Hours of sleep per night           | RA via activity tracker                                      | Daily           |
| Hours of activity per day          | RA via activity tracker                                      | Daily           |
| Hours of activity per night        | RA via activity tracker                                      | Daily           |
| Hours of sitting upright per day   | RA via activity tracker                                      | Daily           |
| Hours of sitting upright per night | RA via activity tracker                                      | Daily           |
| Daily steps                        | RA via activity tracker                                      | Daily           |

### Quality: Low-Value Care

| Measure                                         | Source                                                                        | Day(s) Obtained |
|-------------------------------------------------|-------------------------------------------------------------------------------|-----------------|
| Use of inappropriate medications in the elderly | RA via EHR/MAR/administrative data                                            | Daily           |
| Use of foley catheter                           | RA via MD/RN for home patients; EHR review for inpatients/administrative data | Daily           |
| Use of restraints                               | RA via MD/RN for home patients; EHR review for inpatients/administrative data | Daily           |

### Patient Functional Status and Quality of Life

| Measure                                 | Source         | Day(s) Obtained           |
|-----------------------------------------|----------------|---------------------------|
| EuroQol -5D-5L                          | RA via patient | Admission, discharge, +30 |
| SF-1                                    | RA via patient | admission, discharge, +30 |
| Activities of daily living              | RA via patient | admission, discharge, +30 |
| Instrumental activities of daily living | RA via patient | admission, discharge, +30 |
| Patient Health Questionnaire-2          | RA via patient | Admission, discharge, +30 |
| PROMIS Emotional Support Short Form 4a  | RA via patient | Admission, discharge, +30 |

731 **Patient and Family Experience**

| Measure                         | Source           | Day(s) Obtained                        |
|---------------------------------|------------------|----------------------------------------|
| Picker Experience Questionnaire | RA via patient   | Within 30 days of discharge            |
| Global satisfaction             | RA via patient   | Within 30 days of discharge            |
| Recommend care                  | RA via patient   | Within 30 days of discharge            |
| Qualitative interviews          | See Below        | Within 30 days of discharge            |
| Caregiver burden (Zarit)        | RA via caregiver | Admission, Within 30 days of discharge |

732 **Process Measures**

| Measure                                                                       | Source        | Day(s) Obtained |
|-------------------------------------------------------------------------------|---------------|-----------------|
| Number of RN visits, in-person                                                | RA via RN/EHR | Daily           |
| Number of RN visits, virtual                                                  | RA via RN/EHR | Daily           |
| Number of RN visits, total                                                    | RA via RN/EHR | Daily           |
| RN travel time                                                                | RN            | Daily           |
| Failed connectivity, %                                                        | RN            | Daily           |
| Number of “on call” MD interactions (video or phone)                          | RA via MD     | Daily           |
| Duration of 1 st RN visit                                          | RA via RN     | Daily           |
| Duration of subsequent RN visit, in-person                                    | RA via RN     | Daily           |
| Duration of subsequent RN visit, virtual                                      | RA via RN     | Daily           |
| Other metrics captured on the clinician process survey and nursing visit form | RA via RN     | Daily           |
| Insufficient handoff                                                          | RA via RN     | Daily           |
| Documentation error                                                           | RA via RN     | Daily           |
| Equipment malfunction                                                         | RA via RN     | Daily           |

734 **Covariates of Interest**

| Measure                                      | Source                  | Day(s) Obtained |
|----------------------------------------------|-------------------------|-----------------|
| Age                                          | RA via EHR a | Admission       |
| Gender                                       | RA via EHR              | Admission       |
| Race/ethnicity                               | RA via patient          | Admission       |
| Primary language                             | RA via EHR              | Admission       |
| Health insurance status, public/private/none | RA via EHR              | Admission       |
| BMI                                          | RA via EHR              | Admission       |
| Comorbidities, type and #                    | RA via EHR and H&P      | Admission       |
| Partner status                               | RA via patient          | Admission       |
| Education                                    | RA via patient          | Admission       |
| Zip code                                     | RA via EHR              | Admission       |
| Employment                                   | RA via H&P              | Admission       |
| Smoking status                               | RA via H&P              | Admission       |
| Medications used as outpatient, #            | RA via EHR              | Admission       |
| DNR/I code status                            | RA via H&P              | Admission       |
| Lives alone                                  | RA via patient          | Admission       |
| Home health aide prior to admission          | RA via patient          | Admission       |
| Elective and urgent admissions in the        | RA via EHR and          | Admission       |

|                                                               |                                                                                 |           |
|---------------------------------------------------------------|---------------------------------------------------------------------------------|-----------|
| previous year, #                                              | patient                                                                         |           |
| ED visits in the previous 6 months, #                         | RA via EHR and patient                                                          | Admission |
| Interqual disease-specific leveling                           | MD                                                                              | Admission |
| PRISMA-7                                                      | RA via patient                                                                  | Admission |
| Eight-item Interview to Differentiate Aging and Dementia      | RA via patient or proxy                                                         | Admission |
| Would you be surprised if this patient died in the next year? | RA via MD                                                                       | Admission |
| BRIEF health literacy screening tool                          | RA via patient                                                                  | Admission |
| Readmission risk score on discharge (HOSPITAL)                | RA via EHR                                                                      | Discharge |
| Admitting diagnosis                                           | RA via EHR/MD                                                                   | Admission |
| Admission source                                              | RA via EHR/MD                                                                   | Admission |
| COVID case count on day of admission                          | RA via EHR                                                                      | Admission |
| Degree of rurality                                            | 2010 U.S. Census data, U.S RUCA codes/data files, population density, zip codes | Admission |

a: Note that RA will recheck covariates after MD H&P completed to ensure comorbidities and other covariates correctly captured

The following data will be collected from intervention arm subjects only (patients, caregivers, and clinicians)

| Measure                                                          | Data sources                                                                                                                         | Day(s) Obtained                                                                                               |
|------------------------------------------------------------------|--------------------------------------------------------------------------------------------------------------------------------------|---------------------------------------------------------------------------------------------------------------|
| RHH admission, daily care, and discharge processes accomplished. | Clinician process measures survey                                                                                                    | Twice a week                                                                                                  |
| Perceived acceptability of RHH care                              | Post-discharge semi-structured interviews with RHH clinicians, RHH patients, and caregivers (separate interview guides are attached) | Patients: within 1 month of discharge

Clinicians: Within 60 days after patient enrollment ends at site |
| Perceived safety, quality of care, caregiver burden              | Post-discharge semi-structured interviews with RHH clinicians, RHH patients, caregivers (separate interview guides are attached)     | Patients: within 1 month of discharge

Clinicians: Within 60 days after patient enrollment ends at site |

Video recordings (intervention group only):

- We will video record some of the telemedicine calls between RHH clinicians and rural home hospitalized patients.

- The video recordings will be for internal quality assurance purposes only.
- The video recordings will not be disseminated in any way (not shared externally)
- We have attached the patient interaction monitoring protocol which provides more detail on this process: “ Site Study Team Protocol- Patient Interaction Monitoring”
- 

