## **6.0 BIOSTATISTICAL ANALYSIS**

### **6.1 Quantitative**

We will present descriptive data with counts and percentages, means and 95% CIs, or medians and interquartile ranges, as appropriate.

The primary outcome (hospitalization cost) will be analyzed between arms, adjusted for site as a fixed effect, which accounts for difference across the three sites. . However, we will present cost data as the percentage of change in mean costs from control (rather than absolute difference) because of the sensitive nature of these data. The primary outcome will be assessed using a generalized linear model assuming a gamma distribution with a log link, given the skewed nature of cost, with treatment arm (control arm as the reference group) and site as fixed effects. The exponential of the treatment effect in this gamma regression model exactly equals the effect of interest (the percentage change from control). Patient characteristics should balance out across the two arms due to randomization, but if not, in the gamma regression, we will adjust for any of the follow patient characteristics that differ across arms: sex, age (continuous), education, and comorbid condition count (continuous). We *a priori* plan to also adjust for COVID case burden at each hospital only if COVID impacted home hospital operations. If the degree of rurality was different between patients at different sites, we *a priori* plan to adjust for degree of rurality.

We will use this same multivariable regression approach for secondary outcomes, using logistic regression for binary outcomes (e.g., readmissions) and negative binomial regression for count outcomes such as days at home, and non-transformed linear regression for normally distributed continuous outcomes (e.g., days at home), as appropriate. Given the multiple comparisons, we will use the Benjamini-Hochberg method for multiple comparisons for the secondary outcomes, with 0.2 as a prespecified false discovery rate.

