Secondary outcomes require slightly larger samples sizes at 80% power (with Type 1 error of 1%, approximately the type 1 error when using the Benjamini-Hochberg method as noted above). For Cost, discharge to 30-days, using a gamma regression model similar to total costs, with 66 patients in each arm, we have 80% to see an expected 65% reduction in the mean for intervention to control (we assume the over-dispersion parameter for the gamma distribution variance is 2.8 as seen from our preliminary data). For number of hours per day laying down (equivalently, % of day Lying down), using a negative binomial regression model with a logistic link with treatment and site effects, with 66 patients in each arm, we have over 90% to see an expected 65% reduction in the number of hours lying down for intervention to control (we assume the over-dispersion parameter for the negative binomial distribution is 1.4 as seen from our preliminary data). For percent with 30-day readmission, using logistic regression model with treatment and site effects, with 66 patients in each arm, we have 80% to detect on odds ratio of 0.25 for intervention on control (assuming the percent 30 day readmission in controls is 23% as seen in preliminary data). For the number of days at home, using a log-normal distribution with treatment and site effects, with 66 patients in each arm, we have over 80% to see an expected 65% increase in the number days at home for control to intervention (from 29 days to 48, days assuming the over-dispersion parameter for the negative binomial distribution is 1.4).

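### The secondary-outcome models never use the prior-utilisation counts that the trial already collects: a missed gain in precision, not a bias

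*Protocol*

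**What the plan says.** The Covariates of Interest table (Protocol, section 5.5.3) lists two counts of earlier hospital use, both obtained at admission: "Elective and urgent admissions in the" previous year, and "ED visits in the previous 6 months". Both are drawn from the health record and from the patient.

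Section 5.5.2 makes hospital use after discharge a secondary outcome in three forms: "Total cost, discharge to 30-days post discharge", unplanned readmission within 30 days, and days at home over the same 30 days.

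Section 6.1 fixes the primary model as a gamma regression with a log link, "with treatment arm (control arm as the reference group) and site as fixed effects". If randomisation leaves an imbalance, the analysts will "adjust for any of the follow patient characteristics that differ across arms: sex, age (continuous), education, and comorbid condition count (continuous"). COVID burden enters only if it affected operations, and rurality only if it differed between sites. The section then says: "We will use this same multivariable regression approach for secondary outcomes". Neither utilisation count is named in any model.

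For 30-day cost the power analysis takes 66 per arm, a 65% reduction, a type 1 error of 1% and 80% power, and adds: "we assume the over-dispersion parameter for the gamma distribution variance is 2.8 as seen from our preliminary data".

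**The concern.** Three of the four secondary outcomes measure hospital use after discharge, and the trial holds a record of each patient's hospital use before the index illness. That record is a natural candidate for a prognostic covariate, yet the adjustment rule leaves it out. The rule also fails on its own terms: if prior admissions happened to differ between arms, section 6.1 would not allow adjustment for them, although it would allow adjustment for education.

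What is at stake is the width of the interval for 30-day cost, which has the larger of the two gamma dispersions in the plan (2.8, against 1.2 for the primary outcome), and protection against chance imbalance in a variable close to the outcome. A covariate of this kind has to be fixed before the unblinded data are seen if it is to be credible.

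**Working it through.** **Inputs from the Protocol, Power analysis:** 66 per arm; ratio of means 0.35 (a 65% reduction); gamma dispersion 2.8; type 1 error 1%. Sidedness is not restated for the secondary outcomes, so I take two-sided, as for the primary outcome (z = 2.576).

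**Assumed input:** R², the share of residual variance explained by the prior-admission count. The protocol gives no value. I show 0 to 15%.

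**The plan's own figure first.** For the Wald test on the log ratio:

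- SE = sqrt(2 × 2.8 / 66) = 0.291
- |ln 0.35| = 1.050
- Power = Φ(1.050 / 0.291 − 2.576) = 84.8%

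The stated 80% is therefore conservative; on these inputs 80% needs 60 per arm. Simulating the gamma model with site (4,000 runs) gave 84.9% to 85.8%. The same simulation rejected in 1.5% to 2.0% of runs with no effect, so its power is, if anything, slightly flattering.

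**With the covariate.** SE = sqrt(2 × 2.8 × (1 − R²) / 66). The equivalent total sample is 132 / (1 − R²).

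| Assumed R² | SE | Power at 66 per arm | Equivalent total N |
|---|---|---|---|
| 0 | 0.291 | 84.8% | 132 |
| 5% | 0.284 | 86.9% | 139 |
| 10% | 0.276 | 88.9% | 147 |
| 15% | 0.269 | 90.9% | 155 |

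The gain is 2 to 6 percentage points of power, or the equivalent of 7 to 23 patients. The standard error falls by 2.5% at R² = 5% and by about 8% at R² = 15% (1 − sqrt(0.85) = 0.078).

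**Chance imbalance.** On the same approximation with R² = 10%, an imbalance of one standard error in the covariate moves the log cost ratio by sqrt(0.10 × 2.8) × sqrt(2/66) = 0.092, or about 10% on the ratio. The present model leaves that shift in the estimate.

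**Target of estimation.** With a log link and randomised arms, adding a baseline covariate leaves the ratio of means as the target, so the percentage change that section 6.1 wants to report is preserved. The same is not true of the odds ratio for readmission, which is why the proposal does not extend to that outcome.

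**Days at home.** I give no figure. Section 6.1 names this outcome under both negative binomial and linear regression. The power analysis uses a log-normal distribution with a negative binomial dispersion, and plans for 48 days when section 5.5.2 defines a 30-day window. A gain computed on those inputs would mean little.

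**The case against.** The best reply is that this is a preference, not an error. Omitting a prognostic covariate from a randomised comparison biases nothing and contradicts nothing in the protocol, and a table of covariates of interest does not promise that each will enter a model. That stands, and it sets the weight of the point. But section 6.1 does state a definite adjustment rule, so it is fair to say that the rule passes over a promising variable.

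A reader might infer that the counts are the pre-trial values of the outcomes themselves. They are not. The outcomes are cost and days at home over 30 days; the counts are admissions over a year, elective ones included, and emergency visits over six months. The protocol's data tables include no baseline cost and no baseline days at home. The counts are related predictors and no more.

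A reader might also infer that the 30-day cost comparison is underpowered without the covariate. On the protocol's inputs it already exceeds its stated 80%.

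Three practical objections have force:

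- **Source.** The counts come from the record and the patient together, and covariates are rechecked after the admission history. Nothing shows that the record-based part is stored separately, or that three health systems in two countries capture earlier use alike.
- **Index episode.** Early-transfer patients are already inpatients at randomisation, and others enter through the emergency department, so the index episode could be counted by mistake. Defining the count as admissions before that episode deals with this.
- **Gamma model.** Patients with no hospital use after discharge could have zero cost, which a gamma distribution cannot take. The power figures accept the protocol's model as stated.

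**Conclusion.** The point holds as a minor one. The models omit utilisation counts that are already collected and are plausibly prognostic for hospital use after discharge, and the adjustment rule would exclude them even if they were imbalanced. The consequence is some lost precision, not bias.

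For 30-day cost the gain would be from 84.8% power to between 86.9% and 90.9%. This rests on an assumed R² of 5% to 15% that the protocol neither supports nor contradicts, on a two-sided 1% test, and on the gamma model with dispersion 2.8. If R² is zero there is no gain. For days at home the gain cannot be sized until the protocol settles that outcome's model. The documents do not support a claim that the present results would be invalid or that the planned sample is too small for 30-day cost.

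**What to change.** In section 6.1, pre-specify log(1 + number of admissions in the year before the index episode) as a fixed covariate in the 30-day post-discharge cost model, entered whatever the observed balance. Define the count as excluding the index stay and as taken from records dated before randomisation. One count is enough; using admissions alone keeps the price to a single parameter.

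Use the same covariate for days at home once section 6.1 and the power analysis have been reconciled on that outcome's model.

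The cost is a sentence or two in the analysis section, one degree of freedom among 132 patients, and a data-handling step: the record-based count must be kept separate from what the patient reports, and the sites should confirm that they can extract it in the same way.
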